## 10.3 Confidentiality [27]

A deidentifying study number will be assigned to each participant. This code will be maintained in a secure REDCap database accessible only to the Investigators. Others working with the data will only have access to the study number.

The study will be conducted in accordance with applicable Privacy Acts and Regulations. All information will be stored securely at the participating hospital sites and will only be accessible to people directly involved with the study. Personal data identifying tpatients will be held securely at the participating hospital sites in a locked filing cabinet requiring authorised key pass access for research team.

# 11. Statistical Considerations

## 11.1 Outcomes [12]

*Primary Outcome*

Results from the Full Blood Count for Haemoglobin levels will be collected from local laboratories

*Secondary Outcomes*

In hospital, post-operative complications measured by Clavien-Dindo scale will be collected prospectively by the research team during planned visits for venesection. Length of hospital stay and 30-days outcomes of; reoperation, re-admission to hospital or mortality will be documented locally and confirmed at the 2 and 4 week follow up visits. Any AE / SAE will be similarly recorded. Follow up visits will document Quality of life and functional assessments by the research staff.

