**7.3.1 Schedule of assessments**

**7.3.2 Study Visits**

Patient assessments will start on admission to hospital on the day of surgery (Day 0). Patients will be randomly assigned to receive either intravenous iron or placebo at skin closure in operating theatres administered by the anaesthetics team, if this is not possible for logistical reasons, the patient will receive the one-off infusion in recovery as per local policy.

During inpatient admission, results from routine blood tests measured at day 1, 2, 4 and 8 (if still an inpatient at this time) will be recorded on the CRF. These will be performed as part of the routine clinical post-operative care. An additional SST blood sample (6-8mL or 1.5 teaspoons) will be collected at the time of the routine blood draws for core laboratory analysis.

Subsequent follow up in outpatient at weeks 2, 4 (+/- 1), 8 (+/- 2), 12 (+/- 2), 16 (+/- 2) from the operation date. Functional and quality of life assessments will be collected at those time points.

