### 11.1.1 Primary Endpoint Change in Hb concentration from baseline to 90 days following randomisation

### 11.1.2 Secondary Endpoints Laboratory:

1. Change in Routine Iron markers
2. Changes in Experimental Iron markers
3. Changes in proteomic and metabolomic profiles.
4. Mental and physical recovery after surgery
5. Complication rate at 30 days post operation
6. Length of hospital stay
7. Re-operations
8. Unplanned re-admission to hospital for complications
9. Days Alive and at Home (DAH) 30 & 90
10. Change in clinical frailty score and activities of daily living (Nottingham extended ADL scale)
11. Changes in Sarcopenia
12. Changes in functional assessments
13. Changes in Quality of life

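### Perioperative group: 30-day outcomes are confirmed at a week-4 visit that can fall as early as day 21, and complications are described as collected in hospital although their endpoint runs to day 30

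*Protocol*

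**What the plan says.** Section 11.1 of the protocol sets out how the clinical secondary outcomes are gathered. Of complications it says: "In hospital, post-operative complications measured by Clavien-Dindo scale will be collected prospectively by the research team during planned visits for venesection". Of the other events it says: "30-days outcomes of; reoperation, re-admission to hospital or mortality will be documented locally and confirmed at the 2 and 4 week follow up visits". It adds that AEs and SAEs are recorded in a similar way.

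Section 11.1.2 lists among the endpoints "Complication rate at 30 days post operation" and, with no time limit attached, "Unplanned re-admission to hospital for complications". The 30-day horizon for readmission therefore comes from Section 11.1 alone.

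The visit timing for the Perioperative group is in Section 7.3.2: "Subsequent follow up in outpatient at weeks 2, 4 (+/- 1), 8 (+/- 2), 12 (+/- 2), 16 (+/- 2) from the operation date". The schedule table in Section 7.3 gives the same one-week tolerance at week 4. It also marks blood tests and adverse events at every visit to week 16.

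**The concern.** A 30-day outcome is complete only when the patient's status through day 30 is known. The protocol names the visits that do the confirming, and the later of the two is scheduled before day 30. A site following the text literally could close the 30-day record while part of the window is still to come.

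The complication endpoint has a second mismatch. Its opening words limit collection to the hospital stay, but its horizon runs to day 30 whether or not the patient has gone home. If a site stops grading at discharge, each patient's observation time equals the length of stay. In this group stay is determined after randomisation and is itself a secondary endpoint. An arm discharged sooner could then appear to have fewer complications because it was watched for less time.

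These outcomes are listed as secondary objectives in Section 4.2, and the background section presents a fall in readmission from 21.8% to 13.8% in an earlier trial as part of the motivation for this one. Section 11.2 plans 20 patients per arm in each surgical cohort, so a few missed events could alter a cohort-level comparison.

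**Working it through.** The protocol gives no figure to reproduce. The check is calendar arithmetic on its own visit windows.

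**Inputs.** Week 4 ± 1 week and week 8 ± 2 weeks, both counted from the operation date (Sections 7.3 and 7.3.2). Horizon: day 30 (Sections 11.1 and 11.1.2).

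**Window in days** = 7 × (week ± tolerance).

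- Week 4: 7 × 3 = day 21 to 7 × 5 = day 35; nominal 7 × 4 = day 28.
- Week 8: 7 × 6 = day 42 to 7 × 10 = day 70; nominal day 56.

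**Days of the 30-day window not yet elapsed at the visit** = max(0, 30 − visit day).

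| Visit | Earliest | Nominal | Latest |
| --- | --- | --- | --- |
| Week 4 | 30 − 21 = 9 | 30 − 28 = 2 | 0 |
| Week 8 | 0 | 0 | 0 |

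As shares of the window, the week-4 shortfall is 9/30 = 30% at the earliest and 2/30 = 6.7% at the nominal date.

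**Permitted days before day 30.** Days 21 to 29 are 9 of the 15 days from 21 to 35.

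**Average shortfall, assuming visits are spread evenly over the 15 days.** (9 + 8 + … + 1)/15 = 45/15 = 3.0 days, or 10% of the window. Among the early visits alone it is 45/9 = 5.0 days. The even spread is an assumption; the protocol says nothing about how visits will fall within the window.

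**Complication collection.** No arithmetic applies. The sentence in Section 11.1 contains two cues: it begins by locating the complications in hospital, and it ties collection to planned blood-sampling visits. In the Section 7.3 table blood sampling continues at weeks 2, 4, 8, 12 and 16, after most patients would be expected to have left hospital. One cue suggests collection ends at discharge, and the other allows it to continue. The 30-day endpoint needs the second reading, but the text does not settle the matter.

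**The case against.** The strongest reply is that nothing is shown to be lost. Events are first recorded locally, and the two visits only confirm them. Adverse events are collected to week 16, Section 9.2 makes death and hospitalisation serious adverse events, and Section 5 follows every patient for 16 weeks. A readmission or death on day 29 is thus reportable and can be dated. No passage says that week 4 is the last check. This stands, and it is why the conclusion is a risk of under-counting. It does not remove the risk: no passage says that AE or SAE records feed these endpoints or that events after discharge receive a Clavien-Dindo grade. Local records may also miss events elsewhere, and Section 11.3 reports difficulty in completing follow-up of rural patients.

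A second reply is that the protocol nowhere says complications are collected only in hospital. That is right. The dependence on length of stay holds only under the stricter reading.

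Three stronger inferences are tempting and should not be drawn.

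- A reader might extend the point to "Days Alive and at Home (DAH) 30 & 90". No passage ties those endpoints to the week-4 or week-12 visit, and the 16-week visit (earliest day 7 × 14 = 98) always falls after day 90. A missed readmission or death would also raise the count of days alive and at home, the opposite direction from under-counting.
- A reader might use the nine-day median stay quoted in the background to say what fraction of the 30 days is observed. That figure comes from a different trial, in abdominal surgery only, and would matter only if collection did stop at discharge.
- A reader might apply the windows to the whole trial. Recovery patients enter four weeks after discharge and have no 2-week visit (Section 7.4), so the operation-date windows do not describe them.

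**Conclusion.** The point holds for the Perioperative group, in limited form. The visit named to confirm 30-day reoperation, readmission and mortality cannot do so on schedule. It leaves 2 days unconfirmed at its nominal date and up to 9 at its earliest, with a mean of 3.0 days under an even spread of visits. Separately, the stated setting for complication collection does not match the 30-day endpoint, and the wording lets sites apply different rules.

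The size given here concerns timing. The documents contain no event rates for days 21 to 30, so neither the number of events missed nor any bias between arms can be calculated. The outcomes affected are secondary; the haemoglobin primary endpoint is untouched. Only the protocol was available, but the mismatch lies in what it fixes about data collection. An analysis plan could not repair it after the event if the data had not been gathered.

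**What to change.** Amend Section 11.1 for the Perioperative group in three respects.

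1. Confirm 30-day complications, reoperation, readmission and mortality by event date at the first contact on or after day 30. A week-4 visit on days 30 to 35 qualifies; otherwise the 8-week visit does so without exception. Keep the 2- and 4-week visits as interim checks.
2. State that Clavien-Dindo grading covers complications to day 30 after operation whether or not the patient has been discharged.
3. Name AE and SAE records as a source for these outcomes.

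No visit is added. The cost is a few CRF fields and somewhat longer recall: confirmation at the 8-week visit comes 42 − 30 = 12 to 70 − 30 = 40 days after the window closes. Dated hospital and SAE records would offset much of that.

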### 11.1.1 Primary Endpoint Change in Hb concentration from baseline to 90 days following randomisation

### 11.1.2 Secondary Endpoints Laboratory:

1. Change in Routine Iron markers
2. Changes in Experimental Iron markers
3. Changes in proteomic and metabolomic profiles.
4. Mental and physical recovery after surgery
5. Complication rate at 30 days post operation
6. Length of hospital stay
7. Re-operations
8. Unplanned re-admission to hospital for complications
9. Days Alive and at Home (DAH) 30 & 90
10. Change in clinical frailty score and activities of daily living (Nottingham extended ADL scale)
11. Changes in Sarcopenia
12. Changes in functional assessments
13. Changes in Quality of life

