## 4.2 Secondary Objectives

Investigate the effect of iron deficiency and anaemia in relation to:

1. Laboratory Outcomes:
   1. Routine Haematology markers of: Hb, MCV, RDW
   2. Routine Iron markers of: Ferritin & transferrin saturations
   3. Experimental Iron markers including: STFR, Hepcidin, Erythroferrone and EPO
   4. Experimental Inflammatory markers including: CrP, IL6 and other cytokines
   5. Proteomic and metabolomic profiles.
2. Mental and physical recovery after surgery
   1. Complications as measured by the Clavien Dindo Scale
   2. Length of hospital stay
   3. Re-operations
   4. Unplanned re-admission to hospital for complications
   5. Days Alive and at Home (DAH) 30 & 90
   6. Clinical frailty score and activities of daily living (Nottingham extended ADL scale)
   7. Sarcopenia as assessed by quantitative skeletal muscle analysis and quantative skeletal muscle changes post intervention (where imaging available)
   8. Functional assessments as assessed by Short Physical Performance Battery; 4 metre gait speed, five time sit-stand test, balance test. Maximal handgrip strength, time to get up and go, or 6-minute walk test
   9. Quality of life measured by SF-36v2 health survey, EQ-5D-5L questionnaire and the POMS questionnaire
3. Adverse events / serious adverse events
   1. Assessment of major adverse cardiac events
   2. Assessment of major adverse limb events
   3. Discharge destination

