## **6. Study Population [9]**

This study will include patients undergoing cardiac surgery (coronary bypass or cardiac valve surgery), vascular surgery (patients with critical limb threatening ischaemia undergoing open and endovascular revascularisation procedures), and abdominal surgery (patients undergoing major open or laparoscopic procedures). All groups where iron deficiency and anaemia have been identified to be high risk and impact patient outcomes. The comparators will be the interventions before and after randomisation of treatment.

- The Perioperative group of patients included if about to undergo major cardiac, abdominal and vascular surgery will be consented prior to surgery (See Section 7.2)
- The Recovery group of patients included 4 weeks after hospital discharge following major cardiac, abdominal and vascular surgery will be consented post-operatively (See Section 7.2)

The Perioperative group will assess the mechanisms of iron deficiency and response to intravenous iron therapy in the perioperative period. The Recovery group will assess the feasibility to test patients physical and quality of life recovery in the post-operative setting and assess if this may differ between iron deficient and iron replete patients.

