## 11.4 Statistical Analysis [20a]

Analyses will be based on all randomised participants. Reporting of research findings will be in accordance with CONSORT guidelines. Baseline demographic data and other participant characteristics will be expressed as means and standard deviations for continuous variables and counts and percentages for categorical variables, with 95% confidence intervals provided for estimates of interest where appropriate. The differences in baseline characteristics will be evaluated by either $\chi^{2}$ or Fisher extract test for categorical variables and an independent samples t-test for continuous variables. Changes in recovery outcome scores will be compared for each participant as the difference between baseline and each specified time points scores with univariate analyses comparing changes in outcome.

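### Length of stay and 30-day post-operative complications are listed as endpoints for both groups, but in the Recovery group they are over, or all but over, before randomisation

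*Protocol*

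**What the plan says.** Section 11.1.2 gives a single list of secondary endpoints. It includes "Length of hospital stay", "Complication rate at 30 days post operation" and "Days Alive and at Home (DAH) 30 & 90", together with re-operations and unplanned re-admission. No item is assigned to one group. Section 11.4 adds: "Analyses will be based on all randomised participants".

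Section 11.1 describes how some of these data are collected. In-hospital complications are gathered prospectively by the research team at blood-sampling visits. Length of stay is recorded together with "30-days outcomes of; reoperation, re-admission to hospital or mortality will be documented locally and confirmed at the 2 and 4 week follow up visits".

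On entry, Section 6 states: "The Recovery group of patients included 4 weeks after hospital discharge following major cardiac, abdominal and vascular surgery will be consented post-operatively". Section 7.4.2 agrees, and places randomisation after the baseline assessment, in the outpatient clinic. Section 5 and one sentence of the Abstract's Methods instead put Recovery treatment four weeks after the operation. The table in Section 7.4.1 marks randomisation and study medication in the first follow-up column rather than the baseline column.

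**The concern.** A randomised comparison is informative only for outcomes that can still change after allocation. The Recovery group enters once the surgical admission is over and about a month has passed. Endpoints anchored to that admission or to the first 30 days after surgery then describe the patient's history at entry.

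Two consequences follow if the list is applied as written. Within the Recovery group, an iron-versus-placebo difference on these items reflects chance imbalance but would appear among the trial's outcomes. If the two groups were combined, a real effect in the Perioperative group would be diluted by patients in whom no effect is possible. In addition, a patient must be alive to enter the Recovery group, so once the window has closed, 30-day mortality counted from surgery is zero in both arms by construction.

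**Working it through.** **Planned size (Section 11.2).** 2 groups × 3 surgical cohorts × (20 + 20) = 240, which matches the stated total. The Recovery share is 3 × 40 = 120, or 50%. The section states that there is no formal sample size calculation, so there is no power figure to reproduce.

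**Timeline.** Let L be the length of the surgical stay in days, counting the operation as day 0. Days left of the 30-day window = max(0, 30 − randomisation day).

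| Reading of Recovery entry | Randomisation day | Days left of 30 | Days left of 90 |
|---|---|---|---|
| Four weeks from discharge (Section 6; Section 7.4.1 baseline column; Section 7.4.2) | L + 28 | max(0, 2 − L) | 62 − L |
| Four weeks from operation (Section 5; a sentence in the Abstract's Methods) | 28 | 2 | 62 |
| Section 7.4.1 table taken literally (baseline plus 4 weeks) | L + 56 | 0 | 34 − L |

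On the discharge reading, L = 0 leaves 2 days, L = 1 leaves 1 day, and L of 2 or more leaves none.

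The protocol gives no expected stay for this trial. As an assumption, take 5, 9 and 14 days, the range of medians and quartiles quoted in the Background for the earlier pre-operative iron trial. That trial covered abdominal surgery only. On the discharge reading:
- L = 5: day 33, with 0 of 30 days left
- L = 9: day 37, with 0 of 30 days left
- L = 14: day 42, with 0 of 30 days left

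**Length of stay.** Treatment is given to outpatients, so the surgical stay has ended before randomisation on all three readings.

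**Days alive and at home.** Section 11.1.2 states no starting point. If the count starts at surgery, the 30-day version has the same 0 to 2 days left as above. For L = 9, the 90-day version has 90 − 37 = 53 days left (discharge reading), 90 − 28 = 62 (operation reading) or 90 − 65 = 25 (literal table). If the count starts at randomisation, both versions can respond to treatment.

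**Collection route.** The Recovery schedule has no 2-week visit and no in-hospital sampling, and consent is taken at the baseline visit. The prospective in-hospital collection in Section 11.1 therefore cannot be carried out for this group.

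**Pooling, if it were done.** With an effect d in 60 Perioperative patients per arm and zero in 60 Recovery patients per arm, the pooled effect is (60d + 60 × 0)/120 = d/2. With equal variances the standard error falls by √2 = 1.41, so the test statistic is multiplied by 1.41/2 = 0.71.

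**Perioperative confirmation visit.** Sections 7.3 and 7.3.2 put the 4-week visit at 28 ± 7 days from the operation, that is, days 21 to 35. Day 21 is 9 days short of day 30, and even the nominal day 28 is 2 days short.

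**The case against.** The strongest reply is that these outcomes were meant for the Perioperative group. Section 11.1 relies on in-hospital sampling and a 2-week visit, which only that group has, and assigning endpoints to groups could be left to a statistical analysis plan. This carries weight as evidence of intent. But no section states the restriction, and the protocol itself fixes an endpoint at 30 days from surgery in a list that covers patients randomised after, or just before, that day.

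A second reply is that the protocol never says it will test these items between Recovery arms. Section 4.2 frames them as effects of iron deficiency and anaemia, and the only outcome comparison that Section 11.4 spells out is change in recovery scores. Descriptive use would indeed be harmless. The items nevertheless stand as endpoints of a randomised comparison without that limit.

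Three stronger readings are tempting and are not supported:

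- **That the groups will be pooled, with a definite loss of power.** Basing analyses on all randomised participants defines the analysis population and does not say that the groups are combined. The protocol describes two separate groups with different purposes. With no stated effect size or power, no power loss can be attributed to the plan.
- **That days alive and at home over 30 days is certainly complete before randomisation.** The heading "Mental and physical recovery after surgery" in Section 4.2 suggests counting from surgery, but the primary endpoint in Section 11.1.1 is counted from randomisation and the protocol does not settle the matter. Re-operation and re-admission likewise have no window in Section 11.1.2.
- **That Perioperative events between an early 4-week visit and day 30 are lost.** Outcomes are also documented locally, adverse events are recorded to week 16, and serious adverse events include death and hospitalisation. Only the scheduled confirmation can come too early.

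**Conclusion.** The point holds for length of stay and for 30-day post-operative complications. In 120 of 240 patients, iron cannot affect the first and can have essentially no effect on the second: 0 to 2 of the 30 days follow randomisation, depending on which timing passage applies and on the length of stay. The 30-day re-operation, re-admission and mortality outcomes in Section 11.1 share the fault if counted from surgery. On the same condition, days alive and at home shares it fully at 30 days and partly at 90.

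The conclusion on length of stay needs only the outpatient setting of randomisation. The conclusion on the 30-day window holds on the discharge reading for any stay of 2 days or more, and nearly holds on the operation reading. The 5-, 9- and 14-day stays are illustrative. Dilution arises only if the groups are pooled.

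This should be fixed, but it does not threaten the trial's main result. Only secondary endpoints are affected, and the primary haemoglobin endpoint is counted from randomisation.

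**What to change.** 1. In Section 11.1.2, limit length of stay, 30-day complications and the surgery-anchored 30-day re-operation, re-admission and mortality outcomes to the Perioperative group. In the Recovery group, report them only as baseline characteristics.
2. State the starting point of every remaining time-based endpoint. In the Recovery group, count days alive and at home (30 and 90), re-admission and re-operation from randomisation.
3. Reconcile the passages on Recovery timing: the Abstract's Methods, Section 5, Section 6, the table in Section 7.4.1 and Section 7.4.2.
4. Minor: in the Perioperative group, confirm 30-day outcomes on or after day 30, at the existing 8-week visit or by a record check.

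The cost is protocol wording. No visits or patients are added. The surgery-anchored endpoints will rest on 120 patients instead of a nominal 240, but those are the patients in whom treatment can influence them.
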